## Abstract

Electroconvulsive therapy (ECT) is commonly used to treat treatment-resistant depression (TRD). However, our knowledge of the ECT-induced molecular mechanisms causing clinical improvement is limited. To address this issue, we developed the single-center, prospective observational DetECT study (“Multimodal Biomarkers of ECT in TRD”; registered 18/07/2022, www.clinicalTrials.gov, NCT05463562). Its objective is to identify molecular, psychological, socioeconomic, and clinical biomarkers of ECT response in TRD. We aim to recruit *n* = 134 patients in 3 years. Over the course of 12 biweekly ECT sessions (± 7 weeks), participant blood is collected before and 1 h after the first and seventh ECT and within 1 week after the twelfth session. In pilot subjects (first *n* = 10), additional blood draws are performed 3 and 6 h after the first ECT session to determine the optimal post-ECT blood draw interval. In blood samples, multiomic analyses are performed focusing on genotyping, epigenetics, RNA sequencing, neuron-derived exosomes, purines, and immunometabolics. To determine clinical response and side effects, participants are asked weekly to complete four standardized self-rating questionnaires on depressive and somatic symptoms. Additionally, clinician ratings are obtained three times (weeks 1, 4, and 7) within structured clinical interviews. Medical and sociodemographic data are extracted from patient records. The multimodal data collected are used to perform the conventional statistics as well as mixed linear modeling to identify clusters that link biobehavioural measures to ECT response. The DetECT study can provide important insight into the complex mechanisms of ECT in TRD and a step toward biologically informed and data-driven-based ECT biomarkers.

## Introduction

Major depressive disorder (MDD) is among the most prevalent disorders worldwide [1, 2]. Its 12-month prevalence is ~ 11% and women are affected twice as often as men [3, 4]. It is associated with high personal and socioeconomic costs, also through as well as an elevated morbidity compared to the general public [5–7]. In addition, patients with MDD experience higher cardiovascular and metabolic comorbidities, which contribute to the observed excess mortality [6, 7]. MDD is an episodic disorder and recurrence affects 40–50% [8]. A chronic course of disease (> 24 months) is found in about 25% of MDD subjects [9]. While a number of effective treatments exist, a high proportion of MDD patients do not sufficiently respond to current therapies. Treatment resistance (treatment-resistant depression, TRD) affects about 30% of even patients and is accompanied by higher rates of psychiatric and somatic morbidity as well as mortality [10–12]. TRD definitions are somewhat heterogeneous [13–15], yet the most common one is a lack of clinically meaningful improvement (non-response) following two antidepressant drugs administered in an appropriate dosage and duration [13, 16–18]. This definition is shared by the U.S. Food and Drug Administration (FDA) [19] as well as the European Medicines Agency [20] and the recent German federal depression treatment guidelines [21]. TRD is an important medical and societal issue [22], especially taking the globally rising incidence into account [23–25]. One in three TRD patients attempts suicide at least once in their lifetime, which is twice as high as in treatment-responsive depression [26]. TRD patients use health services more frequently and generate high healthcare costs, both at the absolute level as well as proportionally to the overall costs related to depression [27–29].

Beyond conventional pharmaco- and psychotherapy, neurostimulation techniques such as electroconvulsive therapy (ECT) are widely available, safe, and powerful treatment options in psychiatry [30–33]. About 80% of all ECTs are performed in patients with MDD [34, 35]. Though ECT should always be preceded by an individual risk–benefit assessment [36], studies and meta-analyses overall report markedly favorable response rates as high as 79% and remission in up to 70% of cases [37–39]. In severe and psychotic depressive episodes, Petrides et al. have even reported remission in 95% of their participants [40]. ECT is also a highly effective treatment option for TRD [37], with an efficacy comparable to the general response rates seen in treatment-responsive depression [41]. Studies and meta-analyses indicate an ECT-related response in 56–85% and a remission in about 48% of patients with prior medication failure or TRD, respectively [27, 41–44]. This response rate in TRD is similar to the response rates reported for antidepressant drugs and psychotherapy overall in non TRD patients of about 50–60% [45–51]. It is thus not surprising that the mean effect size of ECT (d ≈ 0.9–1.3) is higher than the one of antidepressants (*d* ≈ 0.37) or psychotherapy (*d* ≈ 0.75) [52–58]. ECT-induced remission is commonly achieved early during treatment (~ 3 weeks after ECT start) [27, 59]. ECT is also known to significantly reduce the risk of suicide [33, 60–62]. Due to the high recurrence rates of up to 81% after acute-phase ECT, maintenance sessions are recommended and performed in gradually decreasing frequency to preserve the initial therapy success [36, 39, 63–68]. During an ECT series, sub-/acute side effects, such as headaches, muscle soreness, nausea, transient hypertension, anterograde and retrograde amnesia (especially ± 3 days around the ECT), and postictal confusion, rarely a delirium, can occur due to the applied current and induced seizure apart from general anesthesia risks [69, 70]. These adverse effects are reversible and short-lived in the majority of cases (< 1 h post-ECT) [69]. The frequency of cognitive or memory side effects is associated with patient and disease characteristics as well as the ECT stimulation paradigm and intensity (e.g., strong, bitemporal stimulation over a long period of time: increased memory disturbance) [70–73]. On average, however, cognitive performance tends to remain the same or improve after ECT treatment [71, 74, 75]. Both magnetic resonance imaging and autopsy studies as well as animal experiments have not demonstrated any organic brain damage due to ECT [76–80]. The balance between strong clinical effects and a tolerable side effect profile makes ECT the gold standard of stimulation methods, provided appropriate patient selection [55, 75, 81, 82].

The therapeutic effect of ECT is thought to come from a combination of short- and long-term effects of the induced epileptic seizures [83]. There is evidence from both preclinical as well as clinical studies on possible molecular/biological mechanisms of action, but not always consistent across studies. The most important findings and hypotheses, however, can be summarized as follows: increase in neurotrophic factors such as brain-derived neurotrophic factors (BDNF) and enhanced neuroplasticity including the formation of new synapses, modulation of neurotransmitter metabolism and subsequent alterations in specific neurotransmission accompanied by modification of epigenetic processes and gene expression changes. Alterations in immune cell composition and cytokine levels and regulation and normalization of hypothalamic–pituitary–adrenal axis dysregulation have been reported. From neuroimaging studies, changes in gray and white matter volumes and normalization of altered functional connectivity are reported [27, 69, 83–85]. To date, however, it is not clear which of these biomolecular processes are relevant for the therapeutic success of ECT [86, 87]. Accordingly, no reliable and clinically applicable biomarkers for ECT are available for MDD and TRD [82, 88–92]. Due to this lack of objective biological measures, clinical decision on ECT is still solely informed by consensus-based treatment guidelines [36, 93, 94]. Similarly, prediction of ECT success is loosely based on a few clinical parameters like episode duration and severity [95, 96], failed prior pharmacotherapy [42, 43], age [97, 98], psychotic features [40], and early symptom improvement [99]. In order to improve clinical decision making and identify MDD patients with an optimal ECT risk–benefit profile, reliable biomarkers and multimodal prognosis models are urgently needed [40, 75]. Although a handful of studies have suggested potential biomarkers [100–113], so far none has proven valid or reliable enough for routine application in day-to-day care.

We have initiated the DetECT study to improve our understanding of the molecular mechanisms contributing to response to ECT in TRD and to discover novel biomarkers for clinical application. Our study relies on a multilevel data structure and multiomics approach including novel potential biomarkers such as: (i) neural cell-derived exosomes, as they hold the potential to serve as peripheral biomarkers mirroring ECT-induced molecular changes in the brain [114–117]; and (ii) purinergic signaling dynamics, potentially modulating immune mechanisms linked to treatment resistance and ECT response [118–121]. Our multidimensional data collection is described below and acknowledges the inherent complexity of MDD and the subsequent biobehavioral changes and patterns evoked by ECT. Ultimately, future biomarkers will likely be a cluster of molecular, behavioral, and clinical measures rather than one single parameter [70, 99].

## Methods

The DetECT study was initiated at the Max Planck Institute of Psychiatry’s (MPIP) research clinic in 2022. All study documents have been approved by the local ethics committee of the Ludwig-Maximilians-University Munich (Project registration number: 21–1087); see also https://www.psych.mpg.de/detect. The study is enrolled with the U.S. National Institute of Health (NIH) clinical study register www.ClinicalTrials.gov (Study ID: NCT05463562, registration date 18/07/2022). The project is conducted in strict accordance with all relevant national and international regulations including the Declaration of Helsinki. A detailed schematic of the study design can be found in Fig. 1.

**Fig. 1 Fig1:**
[figure not shown]
Overview of serial blood draws and psychometry in the DetECT study. In the study’s main phase, blood draws are performed before and after the first and seventh as well as within 1 week after the twelfth ECT session. To estimate clinical response and side effects over time, participants are asked weekly to complete four standardized self-rating questionnaires on depressive and somatic symptoms (Patient Health Questionnaires 9 and 15, Questionnaire on Mental Capacity, Beck Depression Inventory II). Foreign ratings are obtained thrice by a standardized clinical interview (Montgomery-Åsberg Depression Rating Scale, Hamilton Rating Scale for Depression, Global Assessment of Functioning) (created with www.Biorender.com)

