## Study design and population

The DetECT project has a prospective and exploratory design. Recruitment is planned to last 3 years. The study is conducted exclusively in adult (≥ 18 years) and legally competent severely depressed in-patients receiving treatment at the MPIP’s research clinic in the form of ECT. The study design is purely observational. Therefore, both the diagnostic and treatment process including the mode of ECT administration as well as pharmacotherapy is determined solely by the attending psychiatrist in joint decision with the patient based on the overall clinical situation in accordance with the German depression treatment guidelines [21]. Diagnosis is made by a trained psychiatrist in compliance with the depression criteria of the International Classification of Diseases 10th revision (ICD-10). Patients included in the study suffer from TRD that is defined in accordance with the FDA and EMA guidelines, i.e., two or more failed antidepressant treatments in adequate dosing and duration. Depression severity is evaluated via standardized self- and clinician ratings, as described later in detail. Inclusion and exclusion criteria are listed in Table 1.

**Table 1 Tab1:** DetECT eligibility criteria

Inclusion criteria
Age ≥ 18 years, legally competent, and desire to participate
Diagnosis of a depressive episode according to the ICD-10
Severity is confirmed using self- and foreign-rating psychometry
Treatment resistance (i.e. ≥ 2 failed antidepressant treatments)
Clinical indication and upcoming electroconvulsive therapy
Signed electroconvulsive therapy informed consent form
Signed informed consent documents for the DetECT study
Signed consent and participation in MPIP’s biobanking project
Proficient German language and communication skills
Exclusion Criteria
Age < 18 years (minor) or no desire to participate
Legal supervision or acute legal incompetence
Pregnancy and/or breastfeeding
Pervasive developmental disorders and/or intellectual disability
Acute substance abuse (e.g., alcohol, prescription, or illicit drugs)
Severe neurological disease (e.g., severe organic brain damage)
Acute or serious general illness (e.g., relevant anemia requiring transfusion)

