In study participants, serial venous blood draws (prior fasting: ≥ 6 h) are performed before and after the first and seventh as well as after the twelfth ECT session. A detailed schematic of the study design is given in Fig. 1. Pre-ECT blood draws with a total volume of 36 ml include collection of ethylenediamine tetra acetic acid (EDTA) (Sarstedt, S-Monovette® K3 EDTA) and serum (Sarstedt, S-Monovette® Serum Gel) tubes as well as PaxGene Blood RNA Tubes (Qiagen) for the extraction and analysis of DNA and epigenetic measures (e.g., methylation patterns), RNA including messenger and micro-RNA (mRNA and miRNA, respectively), neuron-derived exosomes, purines, hormones, proteins, electrolytes, metabolic parameters, inflammatory markers, and peripheral blood mononuclear cells (PBMCs). Post-ECT blood draws include only EDTA and serum tubes (Sarstedt) for total of 10 ml. In a subset of *n* = 10 participants, which are recruited at the very beginning of the study’s field phase (DetECT pilot phase), the ECT blood collection after the first ECT consists of three time points (1 h, 3 h, and 6 h post). The rationale for this schedule is to characterize the temporal post-ECT dynamics. This would also allow to discriminate between an immediate ECT-induced release of brain-derived molecules and cells through the blood–brain barrier (fast pathway) or a delayed release via cerebrospinal fluid drainage (slow pathway). To achieve this, the pilot phase materials and data are analyzed with regards to the different multiomics read-outs to determine the optimal post-ECT time point for the study main phase. To reduce batch effects, samples are stored in the MPIP’s biobanking unit in freezers for later analyses with larger sample sizes.

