## Prospective statistical analysis

The statistical analysis of the DetECT study mainly focuses on comparing ECT responders with non-responders (internal control group) within the sample. Clinical response indicated by overall and sub-domain changes in psychometry will serve as main dependent variables and analyses focus on within-subject changes over time. On the one hand, we aim to use variance and correlation analyses (e.g., repeated-measures ANOVA, Pearson’s r and correlation matrices), regression models (e.g., linear or logistic regression), and principal component analysis to first identify both significant main and interaction effects between biobehavioral parameters and treatment response. These analyses will be performed for all measures pre-, during, and post-treatment. Aside from using single parameters and the area under the curve as independent variables, we will employ index and score approaches (e.g., inflammatory indexing and Z scores) to allow combined analyses of functionally connected processes. Following these steps, we plan to employ linear mixed models (LMM) to examine if a single or parameter cluster is linked to remission, treatment response, failure, and side effects. As described above, we will also use single and combined as well as over time parameters, indices, or scores to perform LMM. Factors like the SES, comorbidities, smoking, concomitant pharmacological treatment (both general and psychiatry specific), and mode of ECT application (e.g., right-unilateral vs. left-anterior-right-temporal) will be used as covariates. Multiple comparisons correction will be applied. To further ensure that the identified associations are not only statistically significant, but also represent a relevant underlying biological mechanism, we will report both significance (p value) as well as effect size (e.g., Cohen’s d or comparable measures) in prospective DetECT publications, as recommended for instance by Goodman et al. 2019 [161].

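### The last blood draw is tied only to the twelfth ECT session, so a series that ends earlier leaves no post-treatment sample, possibly for reasons linked to outcome

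*Protocol article*

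**What the plan says.** The Fig. 1 legend sets the main-phase schedule: "blood draws are performed before and after the first and seventh as well as within 1 week after the twelfth ECT session". The Study design and population section gives the same anchor, "before and after the first and seventh as well as after the twelfth ECT session", and so does the Abstract, which describes the course as "Over the course of 12 biweekly ECT sessions (± 7 weeks" on average. None of the three mentions a sample for a series that ends sooner.

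The same section states that "The study design is purely observational", and that diagnosis and treatment, including how ECT is given, are "determined solely by the attending psychiatrist in joint decision with the patient based on the overall clinical situation". Nothing in the article obliges a participant to receive twelve sessions.

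The Prospective statistical analysis section makes responders versus non-responders the main comparison and applies it to measures before, during and after treatment. It begins with simpler methods ("we aim to use variance and correlation analyses (e.g., repeated-measures ANOVA" is the opening) and then moves to linear mixed models. Clinician ratings are set by calendar, in weeks 1, 4 and 7, and self-ratings are weekly.

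**The concern.** The draw after session 12 is the only blood sample taken once the series is over. If the number of sessions follows clinical course, then whether that sample exists may also follow clinical course, and clinical course defines the two groups being compared. The end-of-treatment comparison would then be made in a selected subset.

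The Introduction gives a reason to take this seriously: "ECT-induced remission is commonly achieved early during treatment (~ 3 weeks after ECT start" is its description of timing. Twelve sessions in about seven weeks means roughly two a week, so week 3 is about session 6. A series that ended there would miss both the session-7 and the session-12 draws, and only the two session-1 samples would remain.

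The sample size has no margin for such loss. An analysis plan can choose how to handle missing values, but it cannot recover blood that was never drawn.

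**Working it through.** **1. Reproducing N = 134.** Inputs from the Power calculation section: d = 0.5, α = 0.05, power 0.8. Sidedness, test and allocation are not stated. A two-sided t-test with equal groups needs 128. A two-sided Wilcoxon-Mann-Whitney test, with each group size multiplied by the asymptotic relative efficiency 3/π = 0.955, needs 67 + 67 = 134:

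- effective group size 67 × 0.955 = 63.98
- noncentrality = 0.5 × √(63.98/2) = 2.83; critical t = 1.98; power 0.801

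So 134 is matched by equal groups with every participant contributing, and no allowance for missing samples.

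**2. Loss at random within responders.** Response in treatment-resistant depression is 56–85% (Introduction). The share q of responders without a final sample is an **assumption**; the article gives none. At 56% response, 134 splits into 75 responders and 59 non-responders. With n₁ responders and n₂ non-responders left, noncentrality = d × √(0.955 × n₁n₂/(n₁ + n₂)), with d held at 0.5:

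- q = 0: 75 vs 59, noncentrality 2.81, power 0.80
- q = 20%: 60 vs 59, noncentrality 2.66, power 0.75
- q = 40%: 45 vs 59, noncentrality 2.47, power 0.69

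**3. Loss of the fastest responders.** Further **assumptions**: improvement L is standard normal, responders are the top 56%, the marker correlates ρ = 0.303 with L (chosen so that the complete sample gives d = 0.50), and the missing responders are those with the largest L.

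- Response threshold c = −0.151, density φ(c) = 0.3944
- Non-responder mean of L = −0.3944/0.44 = −0.896
- Complete sample: responder mean 0.3944/0.56 = 0.704; d = 0.303 × (0.704 + 0.896)/0.971 = 0.50
- q = 20%: upper cut 1.216, density 0.1905; responder mean (0.3944 − 0.1905)/0.448 = 0.455; d = 0.303 × 1.352/0.964 = 0.42
- q = 40%: upper cut 0.759, density 0.2992; responder mean (0.3944 − 0.2992)/0.336 = 0.283; d = 0.303 × 1.180/0.963 = 0.37

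The divisors 0.971, 0.964 and 0.963 are the pooled within-group SDs of the marker.

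| Response rate | Power, no loss | Random loss, q = 20% / 40% | Fastest lost, q = 20% / 40% |
|---|---|---|---|
| 56% | 0.80 | 0.75 / 0.69 | 0.61 / 0.44 |
| 85% | 0.52 | 0.50 / 0.48 | 0.38 / 0.28 |

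A separate simulation at 60% response (N = 134, correlation 0.30, t-type comparison) gave d = 0.43/0.40/0.36 and power 0.62/0.54/0.43 for q = 20/30/40%, against 0.79 with everyone included. At 85% response, most of the shortfall comes from unequal groups (114 vs 20) and not from missing samples.

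**4. Sampling and rating schedules.** At two sessions a week, session 1 falls in week 1, session 7 in week 4 and session 12 in week 6, and the one-week window reaches week 7. That lines up with the rating weeks 1, 4 and 7. The blood and rating schedules therefore agree for a series that runs to plan; they separate only when a series is shortened or delayed.

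**The case against.** Five points weigh on the other side.

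- **Early stopping is not documented.** A reader might infer from the three-week figure that early remitters stop and drop out of the final analysis. The article does not say so. The figure concerns when remission occurs in the literature, and the same section mentions maintenance sessions at decreasing frequency after acute ECT, so a remitter may still reach a twelfth session. This stands: the risk follows from the sampling rule, but its frequency is unknown.
- **A bias towards no difference is not established.** In the model above, losing the fastest responders shrinks the contrast, and so does losing the least improved non-responders. Stopping for side effects has no fixed direction, and the mix of reasons is not given. This stands too.
- **Mixed models are already planned.** They retain the earlier draws of a participant whose series was short, and repeated-measures ANOVA is only one example of a first step. This stands against any claim that early stoppers are discarded altogether. It does not remove the point: a mixed model corrects for the missing sample only if the observed data explain the missingness, and someone who stops at about session 6 contributes little.
- **The article is condensed.** A rule for early termination could sit in the full protocol. That is possible. Still, all three descriptions of the schedule give the session-12 anchor and no alternative.
- **A fixed session count has a merit.** It holds exposure constant at sampling, and an end-of-series draw does not. This is a real but small cost, because the session-12 draw is kept for all who reach it.

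**Conclusion.** The point holds as a weakness of the sampling rule. Followed as written, a series that ends before session 12 yields no post-treatment blood sample, in a study where series length is a clinical matter and the main comparison is by clinical response. The missingness may therefore depend on outcome and can distort the end-of-treatment comparison.

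The size cannot be determined from the article. The figures for 20–40% loss are illustrations that rest on an assumed share of early stoppers, an assumed pattern of who they are, and the equation of fastest with largest improvement. The effect is confined to blood measures at the last time point, plus session 7 for those who stop before it. Ratings can continue by calendar, and baseline prediction does not need the final draw. The change is worth making because it is cheap and samples not taken cannot be recovered.

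**What to change.** Keep the draw within one week after the twelfth session. Add: for any acute series that ends earlier, take the final draw within one week after its last session, with the clinician ratings at that visit. Keep the week-7 rating for everyone, whatever number of sessions they received. Record the number of sessions and the reason for stopping.

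In the analysis, base the longitudinal comparison on the already planned linear mixed models, using all available draws with actual time and session number, and not on a complete-case repeated-measures ANOVA. Report how many participants lack each draw, by responder status and reason.

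Cost: a small amendment to the sampling schedule and the analysis wording, plus one visit for those who stop early. Because recruitment began in September 2022, participants before and after the amendment would differ in this respect, and the date should be recorded. Early stoppers would be sampled after fewer sessions, so cumulative exposure would vary with outcome. The number of sessions must therefore be modelled, and a sensitivity analysis restricted to those who reach session 12 reported. Only sampling changes; how many sessions a patient receives is untouched.
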